## **7.8 Quality Control**

Electronic questionnaires will have built-in ranges and automated checks to decrease opportunities to enter incorrect information. Study personnel will be carefully trained to properly

fill out each questionnaire to improve uniformity and accuracy. The data will be transmitted to the centralized database in a timely fashion so that the data can be monitored throughout the study period for errors and tested prior to use.

### ***Protection of Privacy and Confidentiality***

All data will be collected on password protected handheld computers. Personally-identifiable data will be kept separate from study questionnaires and linked only by a study identification number. Project paperwork will remain in a double locked, secure location at the Provincial Health Office once they have been transcribed to the central database, available only to a minimum number of local project staff, and will not be reused or disclosed to any other person or entity except as required by law, for authorized oversight of the research project, or for other research for which the use or disclosure of protected health information would be permitted.

Each community participant will be given a study identification number that can be linked to name only by study staff. All identifiers will be destroyed at the earliest opportunity. Two years after the study results are made public, all records will be destroyed. Data on computers will be permanently deleted. All paper documentation including CRFs and consent forms will be shredded. Nasal and nasopharyngeal swab samples and blood samples will be destroyed after 2 years by being stripped of any identifiers, sterilized by autoclave and thrown away or incinerated.

## **7.9 Data Analysis**

In order to evaluate the primary research question – the vaccine effectiveness of the inactivated trivalent IIV3 vaccine in the elderly - we will use Poisson regression with person-time at risk as an offset. The outcome variable will be the number of influenza associated ARI or SARI events in each given year of life among 2 groups, elderly who have been vaccinated with IIV3 and elderly who have not. The resulting count data will account for multiple outcomes in the same participant. We will also employ GEE methodology to the Poisson regression to account for geographical clustering by cases and correlation between outcomes in individuals with repeated measures. We can control for other predictive variables that may be associated with

underlying disease such as age, co-morbidities and distance to health facility. To reduce any potential non-random loss-to-follow up bias, we will use propensity score matching in addition to controlling for confounders. To address the other primary study question regarding cost, we will obtain estimates of direct and indirect costs from each of the groups and apply differences to the adjusted risks to arrive at the adjusted cost differences between elderly who have been vaccinated and elderly who have not been vaccinated.

In order to measure the effect ARI and SARI have on functional status (secondary objective 2.1) we will compare change in functional status among those that did and did not experience ARIs or SARIs by matching participants to one control when they become sick to see if there is a significant difference in functional status measurements. We will use a nested case control study to compare the two groups. By matching those who experienced a first ARI or SARI with those who had not on age ( $\pm 5$  years), sex, influenza vaccination and most recent functional status measurement ( $\pm 1$  point), we can account for unknown confounders that may cause a change in functional status while controlling for known confounders.

To estimate the incidence of influenza-associated COPD exacerbations among elderly with COPD, we will calculate the total number of laboratory-confirmed influenza-associated COPD exacerbations per total number of COPD patients within our cohort over a year (primary objective 1.3). We will compare the incidence among those that were vaccinated with IIV3 versus those that were not vaccinated with IIV3. In order to account for correlation among repetitive measurements from each individual, we will also employ GEE methodology. This method will also allow us to adjust for underlying confounders such as smoking history and age.

Blood samples will be taken from a select number of participants who will have had IIV3 to test the antibody response of IIV3 among the elderly (objective 2.2). These blood samples will be taken at baseline before receiving the shot, and then again after 28 days (1 month), 180 days (6 months), and 360 days (12 months) later. The blood samples will be tested for HI antibodies. Everyone with a baseline HI assay  $\geq 10$  who has a four-fold increase in HI antibody count post vaccination or who has a baseline HI assay  $< 10$  who has a post vaccination count  $\geq 40$  will be considered seroconverted against influenza. One additional blood draw will be taken after 28 days of subsequent vaccination in the second year to compare the effect of prior vaccination on level of immunological response. We will use a random effects model (RE) to compare blood

samples at the post vaccination dates to the baseline HI assay to determine how long participants vaccinated with IIV3 retain an adequate number of HI antibodies. RE allows us to control for the differences in antibody count amongst all individuals across unequal intervals and obtain a mean distribution. This methodology will also allow us to control for confounders such as age and factors which make participants immuno-compromised.

We will also evaluate a simpler outcome, the incidence rate of RSV among elderly with ARI or SARI over the entire observation period (second-objective 2.3), which should be similar between those that were vaccinated with Influenza IIV3 and those that were not.

Aggregate results may be shared with relevant CDC programs in which the findings of this study may have immediate policy implications. Opportunities for publication will be sought.

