Vaccination: Cohort participants, along with all persons aged 65 years and older in the districts identified by the MOPH for increased IIV3 coverage, will be eligible for influenza vaccination through routine vaccine delivery strategies used by the MOPH. No vaccine will be provided as part of this protocol. The study will be enrolling participants from two districts in Nakhon Phanom, That Phanom and Plapak. According to the Nakhon Phanom Provincial Health Office, the vaccination rate in 2014 was calculated to be 52% and 28% in That Phanom and Plapak, respectively. This VE study will follow a pilot program of the MOPH to increase vaccination among the elderly through a concentrated and focused vaccine campaign in the elderly. This year, due to planned vaccination campaigns, we expect the vaccination rate to be around 50% in both districts. A companion study to this protocol, already underway, will evaluate the coverage achieved by the pilot campaign as well as measure factors associated with receipt of the vaccine in this age group.

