### **4.3 Benefits of the study**

The lack of vaccine effectiveness data among elderly in Thailand may be contributing to the low vaccine coverage in the elderly despite recommendations. Only 14-15% of adults  $\geq 65$  years had been vaccinated against influenza between 2010 and 2012 (46). A longitudinal cohort study assessing IIV3 effectiveness against laboratory-confirmed influenza and the duration of the humoral immune response after subsequent vaccinations will help inform policy. It will also help

close current gaps in knowledge regarding IIV3 effectiveness among the elderly and its cost effectiveness. This study will also determine the incidence of influenza-associated exacerbations of COPD among elderly participants having ARIs in the community and whether IIV3 helped alleviate them and reduced hospitalization rates. Our study will also determine if ARIs and SARIs are associated with a long term negative change in functional status among the elderly. Finally, through this study, the incidence of confirmed-RSV among elderly experiencing ARI or SARI in Thailand will be calculated so that prevention and treatment of RSV among elderly can be reevaluated.

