### **6.2 Duration:**

We will begin recruiting and training health care workers on data collection and laboratory technique in February of 2015 until April 2015 allowing three to four months. Participants enrolled in the study will be followed for two years from June 2015 through June 2017. Patients will be followed for two years as the incidence of influenza and the effectiveness of the annual vaccine composition can vary from year to year, making conclusions from two years more reliable than one alone. Additionally, approximately six more months will be needed for data analysis. The entire study will take place for approximately 2 years and 10 months, and should be completed by December 2017.

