#### **7.1.5 Number of participants**

Sample size for cohort: The cohort sample size is calculated assuming a 50% vaccination rate, 80% power, a probability of committing a type I error of 5% and an incidence of influenza-associated ARI of 6% per year. With an expected VE of 40% based on our population's age and past studies (12, 16, 17), the required sample size is 2,724. Given a 15% loss to follow-up, a total of 3,133 persons should be enrolled, and assuming a 10% refusal rate, a total of 3,446, or, for simplicity, 3,500 individuals need to be selected

These sample sizes were calculated in OpenEpi.com(47) using the Fleiss Method with a correction factor as follows:

Fleiss Method:

$$n_1 = \frac{[Z_{\alpha}\sqrt{(r+1)\bar{p}\bar{q}} + Z_{1-\beta}\sqrt{rp_1q_1 + p_2q_2}]^2}{r(p_1 - q_1)^2}$$

$$n_2 = rn_1$$

where  $n_1$  is the number of cases and  $n_2$  is the number of controls,  $\bar{p}$  is the average exposure in the population,  $\bar{q}$  is  $1-\bar{p}$ ,  $p_1$  is the proportion of cases with the exposure,  $q_1$  is  $1-p_1$ ,  $p_2$  is the proportion of controls with exposure and  $q_2$  is  $1-p_2$ .

To account for the use of a normal distribution to approximate a binary function, a continuity correction is applied to  $n_1$  as follows to calculate the final sample size,  $n_{cc}$ :

$$n_{1cc} = \frac{n_1}{4} \left[ 1 + \sqrt{1 + \frac{2(r+1)}{n_1 r |p_2 - p_1|}} \right]^2$$

$$n_{2cc} = rn_{1cc}$$

where  $n_{1cc}$  and  $n_{2cc}$  are the corrected sample sizes of  $n_1$  and  $n_2$ , respectively.

Sample size for changes in functional status related to ARI or SARI: We will select matched pairs and compare functional status (measured on a 10 point scale by the VES-13) three-four weeks after the onset of an influenza-associated ARI or SARI to a control who has not had an ARI or SARI. As functional status is measured on continuous scale of 1-10, a matched dependent  $t$  test is used to compute sample sizes. We have used the PROC POWER procedure in SAS

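### Section 7.9 gives the primary VE model over two influenza years no study-year term, so VE is biased if both coverage and incidence differ between the years

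*Protocol*

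**What the plan says.** Section 7.9 describes the primary VE analysis as a Poisson regression with person-time at risk as the offset. The outcome is defined thus: "The outcome variable will be the number of influenza associated ARI or SARI events in each given year of life among 2 groups", the groups being the vaccinated and the unvaccinated. GEE is added for geographical clustering and repeated outcomes in one person. The covariates offered are variables related to underlying disease, with age, co-morbidities and distance to a health facility as examples. Propensity score matching is added against non-random loss to follow-up. Study year, season and calendar time do not appear as covariate, stratum or matching factor.

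Section 6.2 sets follow-up from June 2015 through June 2017 and gives as the reason for two years that "the incidence of influenza and the effectiveness of the annual vaccine composition can vary from year to year".

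Vaccination is annual, and section 3.1.4 says the study provides no vaccine. On coverage, the same section reports that "the vaccination rate in 2014 was calculated to be 52% and 28% in That Phanom and Plapak, respectively" and expects about 50% in both districts in 2015 because of the planned campaigns. It gives no figure for the second year.

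**The concern.** Influenza incidence in a year affects vaccinated and unvaccinated people alike. If a larger share of the unvaccinated person-time falls in the heavier year, the unvaccinated rate rises for a reason unrelated to the vaccine, and VE is overstated. If it falls in the lighter year, VE is understated.

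Nothing named in section 7.9 removes this:

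- The offset corrects for how long a person is followed, not for when.
- GEE deals with correlated outcomes. It does not model a shared change in the mean.
- The named covariates describe persons, not periods, and year is not a stated term of the propensity score.
- Year of life, read literally, is age. Nearly every age occurs in both study years, so it cannot stand in for calendar year.

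The pooled VE is the main result. Section 7.9 also applies cost differences to the adjusted risks, so an error would carry into the cost result of objective 1.2.

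**Working it through.** **Inputs from the protocol.** Section 7.1.5: "an incidence of influenza-associated ARI of 6% per year"; coverage 50%; VE 40%; "the required sample size is 2,724". Section 3.1.4: 2014 coverage of 52% and 28%. Section 7.5.2: about 6,000 and 3,000 elderly in the two districts, a 2:1 weighting. The 2014 coverage for the two together is (2×52 + 28)/3 = 44%.

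**Assumptions.** Second-year coverage and the incidence ratio between years (neither is in the protocol); status assigned by year; equal person-time in each year; the same true VE in both years.

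**Step 1: the plan's own figure.** Take 6% in the unvaccinated and 6% × 0.60 = 3.6% in the vaccinated, two-sided 5%, 80% power, 1:1. The Fleiss formula gives 1,245 per group, and 1,327 with the continuity correction, so 2,654 in total. That is 2.6% below the stated 2,724: close, not exact. Reading 6% as the overall rate gives 2,098, so 6% is taken as the unvaccinated rate. The calculation uses one annual incidence and one coverage, so it does not address differences between years.

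**Step 2: what a model without a year term estimates.** With coverage c1, c2 and unvaccinated incidence i1, i2:

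- vaccinated rate = (c1·i1 + c2·i2)(1 − VE)/(c1 + c2)
- unvaccinated rate = [(1 − c1)i1 + (1 − c2)i2]/(2 − c1 − c2)
- estimated VE = 1 − ratio of the two

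Only the ratio i2/i1 matters. If c1 = c2 or i1 = i2, the estimate equals the true VE. Vaccinating the same people in both years with equal follow-up is a case of c1 = c2.

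**Step 3: one case in full.** Coverage 50% then 44%, incidence 4% then 8%, true VE 40%:

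- vaccinated: (0.50×0.04 + 0.44×0.08)×0.60/0.94 = 0.0552×0.60/0.94 = 3.52%
- unvaccinated: (0.50×0.04 + 0.56×0.08)/1.06 = 0.0648/1.06 = 6.11%
- ratio 0.576, estimated VE 42.4%

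With a true VE of 0%, the ratio is 5.87/6.11 = 0.961 and the estimate is 3.9%.

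**Step 4: range.** Year-1 coverage is 50%. Entries are estimated VE in % when the true VE is 40%, with the estimate for a true VE of 0% in brackets.

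| Year-2 coverage | Incidence ×2 | Incidence ×1/2 | Incidence ×3 | Incidence ×1/3 |
|---|---|---|---|---|
| 50% | 40.0 (0.0) | 40.0 (0.0) | 40.0 (0.0) | 40.0 (0.0) |
| 44% | 42.4 (3.9) | 37.5 (−4.1) | 43.5 (5.9) | 36.3 (−6.2) |
| 40% | 43.9 (6.5) | 35.8 (−6.9) | 45.8 (9.7) | 33.7 (−10.6) |
| 60% | 35.8 (−7.0) | 43.9 (6.5) | 33.6 (−10.7) | 45.7 (9.6) |
| 30% | 47.9 (13.2) | 31.2 (−14.7) | 51.5 (19.2) | 26.4 (−22.7) |
| 70% | 30.9 (−15.2) | 47.7 (12.8) | 25.7 (−23.8) | 51.1 (18.5) |

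**Step 5: with a study-year term.** A Poisson fit to the expected counts (2,724 person-years in each year) returned the true VE in every scenario fitted, for both 40% and 0%. The precision for a true VE of 40% and incidence 6% then 12%, as 95% intervals without allowance for clustering:

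| Coverage | Without year term | With year term |
|---|---|---|
| 50% then 50% | 40.0 (26.4 to 51.1) | 40.0 (26.4 to 51.1) |
| 50% then 40% | 43.9 (30.8 to 54.5) | 40.0 (25.9 to 51.4) |
| 50% then 30% | 47.9 (35.1 to 58.1) | 40.0 (25.0 to 52.0) |

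**The case against.** The strongest reply is that this is an omission a statistical analysis plan could fill. The covariate list in section 7.9 is open, and nothing there forbids a year term. That is fair, and the point should not be read as saying that year is excluded. Still, section 7.9 already fixes the model family, offset, correlation method, type of covariate and time unit. The open list is confined to variables related to underlying disease, and the time unit named is not calendar year.

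Second, the wording can be read in ways that remove the bias. Year of life may have been meant as study year, with separate yearly analyses. The two groups may be fixed sets of people followed equally in both years. Sections 3.1.4 and 6.2 also disagree on whether follow-up lasts one year or two, which must be reconciled. None of these readings is stated, and section 6.2 relies on conclusions from both years. The condition that status is assigned by year therefore has to travel with the finding.

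Third, a reader might infer from the coverage figures that uptake swings widely, and hence that a useless vaccine would often look effective. The documents do not support that. The 52% and 28% are two districts in the same year. The figure in section 4.3 ("Only 14-15% of adults" aged 65 and over) refers to 2010–2012 and is not given for these districts. Applying 28% to the whole cohort in year 2 uses the 2014 value of Plapak, about one third of the sample. That extreme case, with incidence 4% then 8% and no vaccine effect, gives a spurious VE of about 15% and a simulated false-positive rate of 26%. At 44% coverage the simulated rate is 5–8%, near the nominal 5%. This objection stands and limits the size claimed.

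**Conclusion.** The concern holds in conditional form. The primary model in section 7.9 lacks a study-year term although the protocol itself expects the years to differ. VE across both years is biased when status is assigned by year and coverage and incidence both change, in either direction.

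The likely size is modest. For 50% against 44% coverage and a two- to three-fold incidence change, the shift is about 2 to 4 points at a true VE of 40% and 4 to 6 points at a true VE of 0%. For a coverage change of 10 to 20 points and a two-fold incidence change, it is about 4 to 9 points at a true VE of 40%. These sizes rest on assumed second-year coverage and incidence. The documents do not show that the bias will occur, only that the stated model does not guard against it.

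**What to change.** In section 7.9, state that person-time and vaccination status are split by study year, and that study year enters the primary Poisson/GEE model as a categorical main effect. Replace or clarify the year-of-life wording accordingly. Report VE for each year beside the pooled VE, since section 6.2 expects effectiveness to vary too.

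The cost is a sentence or two in the protocol, one degree of freedom and slightly wider intervals: in the 50%-then-40% case above, a width of 25.5 points against 23.7. Contact and illness-onset dates are already collected (Appendices 4c and 4d). Vaccination status must be available for each year.

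Finer calendar periods are optional for the primary model. Monthly terms should not be required for the COPD analysis (objective 1.3), where events will be few.

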### **For secondary objective 2.1 (Functional status)**

Participants will be scored on their VES-13 results every six months. The Vulnerable Elders Survey (VES-13) is a function-based questionnaire that was developed to screen elderly 65 years of age or greater in the community to determine their risk for health deterioration (7, 8). The questionnaire asks elderly to self-report their age, health, limitations in physical function and functional disabilities, and takes an average of less than five minutes to complete(7, 8). This tool can be administered over the phone or in person. Each response to each question on the form has a point value attached ranging from 0 to 3 points, and it is scored by adding up points based on the responses received, up to 10.(8) Scores  $\geq 3$  indicate frailty associated with increased mortality.

In order to measure the impact of the first episode of ARI or SARI on functional status, we will conduct a nested case-control study of participants recovering from an ARI or SARI. Participants who experience their first ARI or SARI after enrollment will be matched with one cohort participant who has not yet experienced an ARI or SARI based on age ( $\pm 5$  years), sex, influenza vaccination and most recent functional status measurement. Interviews will be conducted three to four weeks after the onset of ARI or SARI in the case and both cases and controls will be compared with respect to changes in functional status measurement using a multinomial logistic regression to control for other potential confounders. Beginning from January 2016, when a complete dataset for vaccination and functional status will be available, these interviews will be conducted until the required sample size of 115 matched pairs of cases and controls are met.

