**Documentation of consent for Immunogenicity study**

|                                                                                     |                                                                                                                                            |
|-------------------------------------------------------------------------------------|--------------------------------------------------------------------------------------------------------------------------------------------|
| Participant has read and signed the informed consent form for Immunogenicity study? | 1 Yes
2 No                                                                                                                              |
| If no, please specify the reason for refusal. _____                          |                                                                                                                                            |
| If yes, ask the following baseline questions and record the following data   |                                                                                                                                            |
| Participant's Identification Number (to obtain Influenza records)                   |                                                                                                                                            |
| Participant's Study ID number                                                       |                                                                                                                                            |
| Participant's HN number                                                             |                                                                                                                                            |
| 10. When, if ever, have you received the influenza vaccine in the past?             | Please circle all that apply:
0 Never
1 Last year
2 2 to 4 years ago
3 5+ years ago
77 Do not know
99 Declined to answer |

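### The primary analysis compares vaccinated and unvaccinated people without tying vaccination status to a dose date or season, although doses can fall within follow-up

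*Protocol*

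**What the plan says.** **Model and exposure.** For the primary question, section 7.9 states that "we will use Poisson regression with person-time at risk as an offset". The outcome is the "number of influenza associated ARI or SARI events in each given year of life among 2 groups, elderly who have been vaccinated with IIV3", compared with those who have not been vaccinated. GEE is added for geographical clustering and for "correlation between outcomes in individuals with repeated measures". The section gives no date or season at which a person becomes vaccinated, no post-dose lag, and no rule for events or time before the dose. The brief summary (3.1.1) describes the same comparison of two groups of people over two years.

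**COPD (objective 1.3).** Section 7.9 divides influenza-associated exacerbations by the number of COPD patients in the cohort over a year, then compares vaccinated with unvaccinated patients. This denominator is a headcount.

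**Timing.** Under 3.1.4, "No vaccine will be provided as part of this protocol"; participants use routine delivery. Section 7.5.2 recruits immunogenicity participants from people presenting for vaccine from 15 May 2015. Cohort enrolment is due by June 2015 (3.1.3). Section 6.2 says "Participants enrolled in the study will be followed for two years from June 2015 through June 2017", and justifies two years because "the incidence of influenza and the effectiveness of the annual vaccine composition can vary from year to year". Section 8.1 anticipates the next year's vaccine arriving during the study.

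**Vaccination data.** Cohort forms 4a to 4g and 4i have no item on influenza vaccine receipt or date. Only the immunogenicity form 4h asks, for example, "When, if ever, have you received the influenza vaccine in the past". The methods for objective 2.1 do expect vaccination data: "Beginning from January 2016, when a complete dataset for vaccination and functional status will be available".

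**The concern.** Vaccination is the exposure behind the primary estimate. It is not given at enrolment, so a participant can be under observation and unvaccinated for part of a season and vaccinated for the rest, and can change status in the second season. A comparison of two groups of people does not say where the earlier part belongs.

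Two departures from a clean split are possible. If a vaccinee's whole year counts as vaccinated, unprotected time dilutes VE. If events follow status at onset but the whole year of person-time stays with the vaccinated group, VE is inflated, because that group is credited with time in which it could not record an event. Influenza and vaccination also both follow the calendar. A 'year of life', read literally, is an age-year that straddles vaccine seasons.

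**Working it through.** **Inputs.** From section 7.1.5: 50% vaccinated, 6% influenza-associated ARI per year, VE 40% (rate ratio 0.60, so 6.0% against 3.6%), 80% power, 5% type I error, 2,724 people (1,362 per group) before inflation for losses and refusal. Assumed: f, the share of vaccinees' risk time that falls before protection, with flat risk over the year. The protocol gives no distribution of dose dates.

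**The plan's own figure.** The Fleiss formula, two-sided, with difference 0.024 and mean proportion 0.048, gives 1,245 per group. The continuity correction gives (1,245/4) × [1 + √(1 + 4/(1,245 × 0.024))]² = 1,327 per group, or 2,654. This is 2.6% below the stated 2,724, so the sample size is not the source of the problem.

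**(a) Groups applied as written: vaccinees' whole year counts as vaccinated.**
Observed rate ratio = f × 1 + (1−f) × 0.60, so observed VE = 40% × (1−f).

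**(b) Events split at the dose, time not split (equal groups).**
Observed rate ratio = 0.60 × (1−f) / (1+f).

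Power is for (a): 6% against 6% × observed rate ratio, 1,362 per group, two-sided, continuity-corrected, one year of events.

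| f (assumed) | VE under (a) | Power under (a) | VE under (b) |
|---|---|---|---|
| 0 | 40% | 81.1% | 40% |
| 0.05 | 38% | 76.4% | 46% |
| 0.10 | 36% | 71.2% | 51% |
| 1/6 | 33% | 63.6% | 57% |
| 0.25 | 30% | 53.5% | 64% |
| 1/3 | 27% | 43.4% | 70% |

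For example, at f = 0.25, (a) gives 0.25 + 0.75 × 0.60 = 0.70, and (b) gives 0.60 × 0.75 / 1.25 = 0.36.

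**(c) Events and time both split at the dose.** Vaccinated rate: 0.036 × (1−f) / (1−f) = 0.036. Unvaccinated rate: 0.06 × (1+f) / (1+f) = 0.06. The ratio is 0.60 at every f, so VE is 40% and this source of bias disappears.

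**(d) Objective 1.3.** A headcount of patients cannot be divided at a dose date. Handling (c) is therefore not available there unless the denominator becomes person-time.

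**The case against.** The strongest reply is that section 7.9 does not forbid the right analysis. Annual counts, a person-time offset and GEE for repeated records are all compatible with status by season and time split at the dose. A SAP may also supply the lag and the calendar term; the covariates in 7.9 are given only as examples. And since vaccine was available from 15 May 2015, close to the end of enrolment, pre-dose time may be short.

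Much of this stands, and it rules out several stronger readings that a reader might infer:

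- *Status is fixed in year 1 and carried into year 2.* No passage says so, and the reason given in 6.2 for two years of follow-up points the other way.
- *Dosing ran to November, or to January 2016.* June to November 2014 (3.1.4) is the period of an earlier pilot. January 2016 is when vaccination and functional-status data together are complete; VES-13 is repeated every six months, so its first repeat may set that date. Neither is a 2015 dosing window.
- *The cohort has no vaccination data.* Objective 2.1 expects them, and the 13-digit ID recorded at cohort consent makes record linkage plausible. The missing form item is not itself a source of bias.
- *VE is inflated.* Handling (b) is not described anywhere; it shows only what a half-made split would do.
- *Power collapses.* The table uses one year of events. With two years at 6% per year (12% against 12% × observed rate ratio, 1,362 per group, same formula), power under (a) is about 93%, 86% and 76% at f = 1/6, 1/4 and 1/3. Section 3.1.4 mentions weekly contact for one year and 6.2 says two years, so the basis is itself unsettled.

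What remains is that the text describes groups of people, and following it literally leads to (a). Compatibility with a better analysis is not a commitment to it. The COPD denominator is not compatible with a split at all.

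**Conclusion.** The point holds as a defect in how the primary exposure is defined. It does not show that the study will misclassify exposure. Applied as written, the two groups dilute a true VE of 40% to 40% × (1−f): a loss of 2 to 4 percentage points if f is 0.05 to 0.10, and of 10 to 13 points if f is 0.25 to 1/3. These figures rest on flat risk over the year and on values of f that the protocol does not supply. The direction reverses if events but not time are split. Splitting both removes this bias whatever f is, so the remedy does not depend on knowing f.

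**What to change.** In section 7.9:

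- Define vaccination as time-updated. A participant is unvaccinated until that season's dose, a prespecified post-dose lag is excluded, and the participant is vaccinated afterwards. Split both events and person-time at these points.
- Reset status each season, and replace 'year of life' with study season.
- Include calendar time in the model.
- For objective 1.3, replace the headcount of COPD patients with person-time split in the same way.
- Name the source of cohort vaccination dates: for example, date-level linkage to vaccination records through the 13-digit ID already collected, or a receipt-and-date item on forms 4b and 4c.

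The cost is slight extra linkage and analysis work, and a small loss of person-time in the lag window. The planned sample size need not change on this account.
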